## **4. STUDY OBJECTIVES**

### **4.1 Overall Objective**

The general purpose of the DAPA-VOLVO study project is to evaluate the effects of dapagliflozin on top of recommended therapy and in comparison to placebo on volume status and on vascular function as well as its mechanistic interactions from an integrative perspective in clinically compensated heart failure patients after hospitalization/ambulatory care because of an acute decompensated (congestive) heart failure event.

The study results may contribute to a better understanding of the underlying mechanisms that mediate the cardio-protective effect of the drug in heart failure patients.

### **4.2 Primary Objective**

The study evaluates the effects of dapagliflozin on blood volume (BV) profile measured via optimized CO-rebreathing (OpCO) technique and on vascular function assessed via retinal vessel analysis (RVA) and pulse wave analysis (PWA) in clinically compensated heart failure patients after hospitalization due to an acute decompensated (congestive) heart failure (ADHF) event.

### **4.3 Secondary Objectives**

The study also seeks to determine whether the effects of dapagliflozin on blood volume profile and vascular function translates to structural and functional improvements of the heart (e.g. exercise performance) and improvements in patient's health-related quality of life (e.g. KCCQ score) as well as in heart failure related laboratory parameters (e.g. NT-proBNP) in comparison to placebo.

Furthermore, the study aims to provide further mechanistic insight into the cardio-protective effects of dapagliflozin in HF-patients by additionally evaluating body fluid distribution, autonomic function (MSNA), tissue sodium content (Na+-MRI) and novel laboratory parameters for heart failure (e.g. FGF23).

### **4.4 Safety Objectives**

The study aims to assess whether dapagliflozin leads to a differential adverse profile (e.g. incidences of hypotension, renal dysfunction, genital infections (GI) and urinary tract infections (UTI), diabetic ketoacidosis, etc.) and general adverse event profile in comparison to placebo.

## 5. STUDY OUTCOMES

### 5.1 Primary Outcome

The primary study outcome is the mean change in relative plasma volume status ( $\Delta$ PVS) from baseline to 12 weeks of dapagliflozin treatment in comparison to placebo.

**Rationale:** The PVS was shown to be associated with prognostic outcomes in heart failure patients in terms of hospitalization and mortality [9, 10, 37]. Furthermore, the estimated PVS at hospital discharge was independently associated with post-discharge clinical outcomes in 3 different ADHF cohorts [93]. Thus, any therapeutic intervention that leads to an improvement in PVS as reflected by shift towards euvoemia (PVS= 0) may also lead to improved clinical outcomes in HF-patients. Following the 'volume'-based hypothesis, the treatment with dapagliflozin may shift and also stabilize the PVS in HF-patients at levels closer to euvoemia.

### 5.2 Secondary Outcomes

- Blood volume profile (Optimized CO-rebreathing, OpCO) ‡;
- Body water content and distribution (Bioimpedance analysis, BIA) ‡;
- Retinal vessel function (Retinal vessel analysis, RVA) §;
- Arterial stiffness (Pulse wave analysis, PWA) §;
- Endothelial function (Flow-mediated dilation, FMD) §;
- HF-hospitalization (either or: worsening of heart failure, WHF\*) °;
- HF-related quality of life (Kansas City cardiomyopathy questionnaire, KCCQ) °;
- Percentage of patients being within the optimal PVS (% PVSopt #) °;

\* WHF: Requiring intensification of therapy in the ambulatory or hospital setting including i.v. diuretics, i.v. nitrates, or other medications for HF, or institution of mechanical or ventilator support.

# %PVSopt: Percent of patients within proposed optimal PVS divergence interval for HF as defined by the combined divergence interval with the lowest reported hazard ratio (HR) for HF-hospitalization and mortality: -4% to -18% of iPV [9, 10]);

‡ Primary volume-related outcomes, § Primary vascular function-related outcomes, ° Other outcomes;

**Rationale:** The secondary outcomes are add-on study measures, which are directly or indirectly linked to the primary study outcome (PVS) and are supposed to be altered by dapagliflozin treatment according to scientific literature.

Thus, these parameters may help to provide a more detailed mechanistic insight into the effects of dapagliflozin treatment on volume status and vascular function as potential mediators of cardio-protection.

Additionally, the effects of dapagliflozin treatment on selected clinical outcomes will be also assessed and potential associations to measured functional parameters will be evaluated.

### 5.3 Other Outcomes of Interest

Tertiary Outcomes:

- Exercise capacity (CPET: VO2peak, VE/VO2slope, 6MWD) °;
- Left ventricular morphology and function (TTE: LVM, LVEF) °;
- Sympathetic activity (MSNA) °;
- Tissue sodium content (Na-MRI: skin, muscle, cartilage) ‡;
- Renal perfusion and oxygenation (ASL H-MRI and BOLD MRI) °;
- Total amount of albumin and other blood constituents (OpCO) ‡;
- Cardio-renal biomarkers (e.g. FGF23) °;
- Iron metabolic biomarkers (serum ferritin, TSAT, hepcidin) °;

Rationale: The tertiary study outcomes are supposed to be affected by dapagliflozin treatment according to available scientific literature. The selected study measures may provide an even more advanced and partially novel mechanistic insight into the effects of dapagliflozin treatment on cardiac and vascular function. Furthermore, the tertiary outcomes will evaluate whether the treatment with dapagliflozin has beneficial effects on cardiac function (e.g. LVEF) and exercise performance (e.g.  $VO_{2peak}$ ) in comparison to placebo in this particular cohort of heart failure patients.

## 5.4 Safety Outcomes

The following safety outcomes of the main study (V2-V5) are defined:

- AEs/SAEs;
- Renal function (eGFR);
- Incidence/events of hypotension (systolic BP < 90mmHg in 3 consecutive measurements);
- Incidence/events of GI-/UTI-infections;
- Incidence/events of diabetic ketoacidosis (DKA);
- Incidence/events of Fournier gangrene (FG);
- Incidence/events of back pain;
- Laboratory biomarker of heart failure (NT-proBNP);
- Other relevant laboratory parameter;

Rationale: The patient's safety has absolute priority. The defined safety outcome variables are primarily chosen based on the safety reports of previous trials in HF-patients (e.g. DAPA-HF).

Of note, the defined safety outcomes will not be assessed after the end of the main study period (V5).

## 6. STUDY DESIGN

### 6.1 General study design and justification of design

#### 6.1.1 General study design

The DAPA-VOLVO study project is a randomized, double-blind, placebo-controlled parallel-group trial to evaluate the superiority of dapagliflozin on top of recommended therapy in comparison to placebo on blood volume profile and vascular function in clinically stabilized heart failure patients after hospitalization/ ambulatory care because of an acute decompensated (congestive) heart failure event. A total of 80 HF-patients (40 patients per each treatment arm) will be recruited at the University Hospital Zurich.

DAPA-VOLVO- Main study:

The main study will comprise of 5 visits at the study site within the study observation period, albeit V1 will be integrated into V2 whenever logistically feasible. The primary goal must be to follow the planned study frame, however if for particular reasons a study patient can only be enrolled in the short-term post hospitalization phase, e.g. due to the patients wish because of stress overload induced by clinical interventions/procedures during the hospitalization/ ambulatory care phase, a note to file should be generated incl. the reason for the 'postponed' study start.

The relative visit schedule should be maintained as planned (see Fig.1, Table 1).

Important: The study information (SI) must be provided to the potential study candidate at least 24 hours prior to V1. The main study ends after the completion of V5, which also represents the end of IMP-treatment.

DAPA-VOLVO- Advanced session(s):

In order to get a better mechanistic insight into the dapagliflozin effect in HF-patients after an ADHF event an optional advanced session(s) program is implemented. The patients can voluntary choose on the informed consent sheet via check box whether they want to participate or not. The program (Fig. 13) comprises additional tests (e.g. CPET) in close proximity to V2 (V2a) and V5 (V5a).

**At visit 1** (V1, screening visit, -5d to -1d) after signing the informed consent, the patients will be evaluated first against the inclusion and exclusion criteria (see 7.1). Eligible patients will be enrolled into the study and randomized to 12 weeks of daily oral dapagliflozin treatment (10mg/day) or placebo. Also, a short medical anamnesis and a short standard physical examination will be performed including venous and urine sampling for laboratory analysis and the dates for the baseline visit and follow-up visits will be arranged. Of note, V1 will be integrated into V2 whenever this is logistically feasible/possible.

**At visit 2** (V2, baseline visit, -2d to 0d), the primary outcome and secondary/tertiary outcomes will be assessed at baseline (see 9.) after a short medical anamnesis and physical examination. Additionally, the venous blood and urine samples will be collected for laboratory analysis. Of note, the baseline measurement of the primary study outcome (PVS) should be performed  $\leq 48$  hours prior to treatment start (0d).

Treatment start (d0):

The treatment will start after the baseline measurements are finished, however depending on the clinical setting/ status of the patients the treatment start may be delayed but the reason for the delay must be documented (e.g. via note to file). The patients will be introduced to continue the medication for the study duration but to maintain a time gap of at least 12 hours between each drug intake.

**At visit 3** (V3, Follow-up visit, 2w  $\pm$  5d post treatment start), the primary outcome and selected secondary and tertiary outcomes including safety outcomes will be assessed after a short medical anamnesis and physical examination. Additionally, the venous blood and urine samples will be collected for laboratory analysis.

**At visit 4** (V4, Follow-up visit, 6w  $\pm$  5d post treatment start), the visit procedures will be repeated similar to visit 2.

**At visit 5** (V5, Follow-up visit, after 12 weeks ( $\pm$  5d) of treatment), patients will be invited for the final study visit to re-evaluate the primary, secondary and tertiary study outcomes as well as defined safety outcomes similar to baseline visit. At the end of the study, the IMP-treatment will be stopped and regular recommended therapy as clinically indicated will be continued in all patients.

#### **Advanced session(s) (V2a/V5a):**

The study patients who are willing to participate will perform additional tests in the advanced session(s) program (see Fig. 13) either at the same day or in close as possible/ feasible proximity to V2 (V2a) and V5 (V5a) but prior to treatment start. In dependence of the feasibility/capacity, the additional program includes tests to evaluate the exercise capacity, cardiac- and autonomic function as well as MRI-imaging (see also 9.).

#### **DAPA-VOLVO- Follow-U (V6):**

The prospective observational follow-up study will include another optional visit (V6) at the study site to re-evaluate selected outcome measures of the main study 12 months ( $\pm$  2w) after the main study end and treatment stop with the IMP (V5). The patients can decide by marking the corresponding check box on the informed consent sheet, whether they are willing to also participate in the follow-up study or not.

Of note, the follow-up study will be evaluated and analysed separately from the main study (see also 6.1.1, 11.4.1, Fig. 1, Table 1).

**Table 3.** Study tasks and dates (ideal recruitment rate).

| Task                              | Date |
|------------------------------------------|-------------|
| First patient first visit (FPFV)         | 04/2021     |
| Last patient first visit (LPFV)          | 07/2022     |
| Last patient last visit (LPLV)           | 10/2022     |
| First study results (FSR)                | 11/2022     |
| Submission of 1 st manuscript | 01/2023     |

### **6.1.2 Justification of study design**

The study design of the DAPA-VOLVO project follows the actual GCP guidelines [14] for RCTs and is considered as adequate for the current study purpose. The main study limitation is the relative small sample size, however a priori sample size calculation for the primary outcome was performed using a statistical test (MMRM) with a relatively 'robust' analysis to minimize the limitation factor (see 11.2).

## **6.2 Methods of minimising bias**

### **6.2.1 Randomisation**

Eligible patients will be randomized to dapagliflozin treatment group or placebo group in a 1:1 allocation ratio using block randomization. Randomization will be performed with a random computerized algorithm using the secuTrial ® software system via interactive response technology (IRT). The investigator or his/her delegate will contact the IRT after confirming that the patient fulfils all the inclusion and none of the exclusion criteria. The IRT will assign a randomization number to the patient, which will be used to link the patient to a treatment arm and will specify a unique medication number for the first package of investigational treatment to be dispensed to the patient. The randomization list is generated by the secuTrial ® software system and responsible staff at the Clinical Trial Center Zurich. The secuTrial ® software system ensures that the randomization list is concealed from the study team and investigators (unless in case of necessary unblinding as depicted in 5.4).

### **6.2.2 Blinding procedures**

Patients, investigator staff, persons performing the assessments and data analysts will remain blind to the identity of the treatment from the time of randomization until database lock, using the following methods:

1. Randomization data are kept strictly confidential until the time point of unblinding, and will not be accessible by anyone involved in the study.
2. The identity of the treatments will be concealed by the use of investigational treatment that are all identical in packaging, labelling, schedule of administration, appearance, taste and odor.

### **6.2.3 Other methods of minimising bias**

N.A.

## **6.3 Unblinding procedures (code break)**

A code break will be available to the investigator and is supplied by the secuTrial® software system. This code break should be opened only in emergency situations when the identity of the investigational product must be known by the investigator in order to provide appropriate medical treatment. For any patient whose treatment code has been broken the patient must discontinue the study treatment.

## 7. STUDY POPULATION

Patients with a diagnosis of de novo or chronic heart failure and clinically stabilized (planned for hospital discharge) after hospitalization/ ambulatory care because of an acute decompensated (congestive) heart failure (ADHF) event will be enrolled in this study. The total number of participants is 80, studied at one treatment site (University Hospital Zurich). During the enrolment period of 20 months, we expect to include an average of 4.1 patients per month, which corresponds to 1 patient per week (optimal recruitment conditions).

If the planned enrolment goals are not met, the enrolment period may be extended and additional staff allocated to the study and/or another medical study centre within Switzerland or outside might be recruited to guarantee sufficient numbers of enrolled patients for primary study outcome.

### 7.1 Eligibility criteria

#### 7.1.1 Inclusion criteria

Participants fulfilling all of the following inclusion criteria are eligible for the study, for example:

1. Male or female, age of 18 years or older;
2. Patients with documented diagnosis of de novo or chronic heart failure (NYHA II-IV) and clinically stabilized (considered for hospital discharge) after hospitalization/ ambulatory care because of an acute decompensated (congestive) heart failure (ADHF) event;
3.  $\text{eGFR} \geq 30 \text{ mL/min/1.73 m}^2$  (CKD-EPI formula) at enrolment;
4. Provision of signed informed consent prior to any study specific procedure;

#### 7.1.2 Exclusion criteria

The presence of any one of the following exclusion criteria will lead to exclusion of the participant, for example:

1. Contraindications to the class of drugs under study, e.g. known hypersensitivity or allergy to class of drugs or the investigational product;
2. Receiving therapy with an SGLT2 inhibitor within 8 weeks prior to enrolment or previous intolerance of an SGLT2 inhibitor;
3. Participation in another study with investigational drug within the 30 days preceding and during the present study;
4. Type 1 diabetes mellitus;
5. Symptomatic hypotension or systolic blood pressure  $< 90 \text{ mmHg}$  at 2 out of 3 measurements either at visit 1 or visit 2;
6. Coronary revascularization (percutaneous coronary intervention because of STEMI or coronary artery bypass grafting) or valvular repair/replacement within 12 weeks prior to enrolment or planned to undergo any of these operations after randomization;
7. Implantation of a CRT device within 12 weeks prior to enrolment or intent to implant a CRT device during 12 weeks of study observation period if indicated according to the actual guidelines [11];
8. Previous cardiac transplantation or implantation of a ventricular assistance device or similar device, or implantation expected after randomization;
9. HF due to restrictive cardiomyopathy, active myocarditis, constrictive pericarditis, hypertrophic obstructive cardiomyopathy or uncorrected primary valvular disease;
10. Symptomatic bradycardia or second or third degree heart block without a pacemaker;
11. Severe ( $\text{eGFR} < 20 \text{ mL/min/1.73 m}^2$  by CKD-EPI), unstable or rapidly progressing renal disease;
12. Women who are pregnant or breast feeding;
13. Intention to become pregnant during the course of the study;
14. Known or suspected non-compliance, drug or alcohol abuse;
15. Inability to follow the procedures of the study, e.g. due to language problems, psychological disorders, dementia, etc. of the participant;
16. Patients with severely restricted liver function;
17. Patients with recurrent mycotic genital infections;

## **7.2 Recruitment and screening**

Patients will be recruited from the inpatient and outpatient clinics of the University Hospital Zurich (USZ) and the Triemli Hospital Zurich. The Triemli Hospital is located in close proximity to the USZ and the hospital takes over heart failure patients and potential study candidates within the Zurich region. The USZ and the Triemli Hospital work together in a collaborative effort, however the Triemli Hospital will only inform the USZ study team about potential study candidates admitted to the hospital. The USZ study team will then contact the patients and inform about the DAPA-VOLVO trial. Of note, the Triemli Hospital does not serve as an additional study centre and all study relevant procedures (e.g. patient recruitment, patient screening, study visits etc.) will be performed only by the USZ study team at the USZ. Briefly, hospitalized/ ambulatory care patients will be asked if they are interested in participating in the study directly by the physician or a member of the study team. Interested participants will then be invited to the screening visit where the inclusion and exclusion criteria will be checked first. The screening assessments are described in section 9.3. Patients require laboratory results, which are assessed during the screening visit. Patients will receive no payment for study participation other than reimbursement for travel costs.

## **7.3 Assignment to study groups**

Eligible participants will be randomized and assigned to the study groups as described in section 6.2.1.

## **7.4 Criteria for withdrawal / discontinuation of participants**

The following circumstances will require withdrawal/discontinuation of a study participant:

- Withdrawal of informed consent;
- Investigator thinks that continuation would be detrimental to the patient's well-being;
- Pregnancy;

Study drug may be discontinued at the investigator's discretion if any of the following occurs:

- Any severe suspected drug-related AE;
- Any other protocol deviation that results in a significant risk to the patient's safety;

Patients that permanently interrupt study treatment should continue their recommended therapy.

Patients that are excluded from the study due to above reasons will be replaced.

Data and blood samples collected up to the time of withdrawal/discontinuation will be analyzed.

Data will be kept anonymously and all samples will be destroyed after publication of the study results.

The description of follow-up procedures is provided in section 9.2.5.

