## **8.5 Data collection and follow-up for withdrawn participants**

Patients that withdraw from the study drug will be encouraged to participate in all regular study visits and assessments. Patients that withdraw consent will be included in the intention-to-treat analysis with the measurements that have been obtained until the withdrawal.

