### **11.5 Handling of missing data and drop-outs**

Study dropouts will be listed, showing reasons for discontinuation. All patients originally randomized will be included in the intent to treat (ITT) analysis [124] (patients will be assigned to treatment groups

as initially randomized).

Additional patients will be recruited and randomised to replace potential dropouts of the main study in order to maintain sufficient statistical power for the primary outcome analysis.

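### Section 7.4 does not separate stopping study drug from leaving the study and is not reconciled with 8.5, so week-12 PVS after drug stop may be lost

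*Protocol*

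**What the plan says.** Section 7.4 of the protocol contains two lists. The first opens "The following circumstances will require withdrawal/discontinuation of a study participant" and names withdrawn consent, the investigator's judgement that continuing would harm the patient, and pregnancy. The second opens "Study drug may be discontinued at the investigator's discretion if any of the following occurs" and names severe suspected drug-related adverse events and protocol deviations that endanger the patient. After both lists come three rules:

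- On filling vacated places: "Patients that are excluded from the study due to above reasons will be replaced"
- On which measurements enter the analysis: "Data and blood samples collected up to the time of withdrawal/discontinuation will be analyzed"
- On what happens next to the patient: "The description of follow-up procedures is provided in section 9.2.5"

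Section 9.2.5 describes a single final visit for participants who leave early: examination, blood sampling, adverse events, eGFR, blood pressure and NT-proBNP. The CO-rebreathing measurement that yields PVS is not listed.

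Section 8.5 takes another line: "Patients that withdraw from the study drug will be encouraged to participate in all regular study visits and assessments". It ties shortened data to consent alone: "Patients that withdraw consent will be included in the intention-to-treat analysis with the measurements that have been obtained until the withdrawal". Section 8.4 keeps patients who take less than 80% of their drug in the study and in the intention-to-treat (ITT) analysis. Section 11.5 adds "All patients originally randomized will be included in the intent to treat (ITT) analysis" and also provides for replacing dropouts.

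**The concern.** Take a patient who stops tablets at week 3 because of a severe suspected drug reaction. Under 8.5 the site would try to obtain PVS at V4 (week 6) and V5 (week 12). Under 7.4, read with its reference to 9.2.5, the site could hold one closing visit without PVS and randomise a replacement. Section 7.4 does not mention 8.5, so nothing tells the site which route applies. One result would be odd: a poorly adherent patient is followed to week 12 under 8.4, while a patient stopped for a drug reaction is not.

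The situation is foreseeable. Sections 6.3, 7.4, 8.3 and 8.6 all provide for stopping drug. Some of the triggers, hypovolemia and volume depletion, bear directly on PVS, so stopping may be related to the primary outcome. Section 11.4.2 prefers the mixed model because it copes with data missing at random. PVS measured after drug stop would make the primary analysis lean less on that assumption. A replacement patient restores the head count but not the missing outcome, and ITT inclusion cannot recover a value that was never measured.

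**Working it through.** **The passages side by side, for a patient who only stops drug**

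| Question | 7.4, wide reading | 8.5 |
|---|---|---|
| Later visits | one closing visit (9.2.5) | all regular visits, encouraged |
| PVS after drug stop | not listed | part of the regular visits |
| Data used | up to the stop | shortened only if consent is withdrawn |
| Replaced | yes | not stated |

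**Inputs for size.** Section 11.2 gives d = 0.5, two-sided 5%, 80% power and a baseline to week-12 correlation of 0.6. The plan has 40 patients per arm. The plan's figure reproduces: the t-test needs 63.77 per group, rounded to 64, and 128 × (1 − 0.6²) = 128 × 0.64 = 81.92, against the stated 81.9. This supplies the scale only and does not decide the point. No stopping rate and no off-drug PVS course are given, so everything below is assumption.

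**Illustration.** A share q of the dapagliflozin arm stops at random and loses the whole effect by week 12. The as-randomised effect is 0.5 × (1 − q). Data cut at drug stop estimate 0.50. The ratio is 1/(1 − q).

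| q | Patients of 40 | As-randomised effect (SD) | Data cut at stop (SD) | Ratio |
|---|---|---|---|---|
| 5% | 2 | 0.475 | 0.50 | 1.05 |
| 10% | 4 | 0.45 | 0.50 | 1.11 |
| 15% | 6 | 0.425 | 0.50 | 1.18 |
| 20% | 8 | 0.40 | 0.50 | 1.25 |

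**Other assumptions.** Simulation with 4,000 runs, 40 per arm, a baseline-adjusted week-12 comparison, an on-drug effect of 0.50 SD, and stopping in 15% on dapagliflozin and 5% on placebo:

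| Effect after drug stop | Who stops | Full follow-up | Cut at stop | Bias |
|---|---|---|---|---|
| lost | at random | 0.42 | 0.50 | overstated |
| lost | lower PVS, moderate selection | 0.43 | 0.43 | about none |
| lost | lower PVS, strong selection | 0.42 | 0.39 | understated |
| lost | higher PVS, moderate selection | 0.43 | 0.57 | overstated |
| kept | at random | 0.50 | 0.50 | none |
| kept | lower PVS, moderate selection | 0.50 | 0.43 | understated |

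Moderate and strong selection mean correlations of 0.5 and 0.8 between the tendency to stop and the week-12 value given baseline. This simulation uses no intermediate visits. A mixed model with V3 and V4 could recover part of the selection where earlier PVS predicts stopping, so the rows show possible directions and are not forecasts.

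**The case against.** The strongest reply is that 7.4 can be read consistently with 8.5. Its lists have different subjects, the participant in one and the study drug in the other. The replacement sentence covers only patients excluded from the study. The paired term in the data sentence echoes the section heading, which concerns participants. Section 9.2.5 is likewise addressed to people who leave the study. The data sentence says that what was collected is used, not that later data are discarded. Section 8.5 is the specific section on stopping drug.

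Much of this stands, and it rules out stronger readings that a reader might infer:

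- **That 7.4 plainly treats stopping drug as leaving the study.** It lists the two separately. The fault is that the rules after both lists do not say which list they govern, and that the only cross-reference is to 9.2.5.
- **That 8.5 and 11.5 promise full follow-up.** Section 8.5 encourages attendance. Section 11.5 promises ITT inclusion, is silent on off-drug visits and itself replaces dropouts, so it does not contradict 7.4 on replacement.
- **That stopping will be unequal between arms.** Section 3.7 reports discontinuation of 0.2% against 0% for genital infection and 0.2% against 0.1% for urinary infection. Section 3.4.1 reports no difference in volume-depletion, renal or hypoglycemia events. These are other populations and selected reasons, but nothing in the protocol supports 10% to 20%.
- **That numbering the randomisation list 01 to 100 for 80 patients shows how many replacements are intended.** Section 8.1.3 gives no such purpose.

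The reply does not remove the ambiguity. The reference to reasons above follows both lists, and a site has to guess.

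**Conclusion.** The concern holds as an unreconciled ambiguity between 7.4 and 8.5 that could cost week-12 PVS in patients who stop drug. The as-randomised comparison may then be biased. A reader might go further and conclude that the treatment effect is overstated. The documents do not support that: with no stopping rate and no off-drug course, overstatement, no bias and understatement are all possible. The range of 1.11 to 1.25 times the as-randomised effect rests wholly on three assumptions: 10% to 20% stopping in the dapagliflozin arm, stopping at random, and complete loss of effect by week 12. With 40 patients per arm, those shares are 4 to 8 people. The wording should be settled because the remedy is cheap and PVS that was not measured cannot be recovered later.

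**What to change.** Reconcile 7.4 with 8.5:

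1. State in 7.4 that patients who only stop study drug, and are not withdrawn from the study, are handled under 8.5. Their remaining scheduled visits among V3 to V5 include PVS, all data collected after drug stop enter the ITT analysis, and they do not count as dropouts to be replaced under 7.4 or 11.5.
2. Limit the replacement rule, the sentence on data up to withdrawal or discontinuation, and the reference to 9.2.5 to patients who leave the study.
3. Leave the clinical withdrawal criteria as they are. The change must not be worded to keep in the study everyone who has not withdrawn consent, because 7.4 also withdraws participants for pregnancy and on the investigator's judgement. Pregnancy itself appears as study withdrawal in 7.4 and 10.1.2 but as drug discontinuation in 8.6. The sponsor should reconcile those passages.

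The cost is an amendment to wording; the visits are already scheduled. The downside is that including off-drug data may make the reported effect somewhat smaller. Under the illustration, t-test power at 40 per arm (adjusted SD √(1 − 0.36) = 0.8) falls from 79% for 0.50 SD to 70% for 0.45 SD and 60% for 0.40 SD.
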